## Abstract

**Background:**

Implant-based breast reconstruction (IBBR) is the most commonly performed reconstructive procedure in the UK. The introduction of techniques to augment the subpectoral pocket has revolutionised the procedure, but there is a lack of high-quality outcome data to describe the safety or effectiveness of these techniques. Randomised controlled trials (RCTs) are the best way of comparing treatments, but surgical RCTs are challenging. The iBRA (implant breast reconstruction evaluation) study aims to determine the feasibility, design and conduct of a pragmatic RCT to examine the effectiveness of approaches to IBBR.

**Methods/design:**

The iBRA study is a trainee-led research collaborative project with four phases:Phase 1 – a national practice questionnaire (NPQ) to survey current practicePhase 2 – a multi-centre prospective cohort study of patients undergoing IBBR to evaluate the clinical and patient-reported outcomesPhase 3– an IBBR-RCT acceptability survey and qualitative work to explore patients’ and surgeons’ views of proposed trial designs and candidate outcomes.Phase 4 – phases 1 to 3 will inform the design and conduct of the future RCT

All centres offering IBBR will be encouraged to participate by the breast and plastic surgical professional associations (Association of Breast Surgery and British Association of Plastic Reconstructive and Aesthetic Surgeons).

Data collected will inform the feasibility of undertaking an RCT by defining current practice and exploring issues surrounding recruitment, selection of comparator arms, choice of primary outcome, sample size, selection criteria, trial conduct, methods of data collection and feasibility of using the trainee collaborative model to recruit patients and collect data.

**Discussion:**

The preliminary work undertaken within the iBRA study will determine the feasibility, design and conduct of a definitive RCT in IBBR. It will work with the trainee collaborative to build capacity by creating an infrastructure of research-active breast and plastic surgeons which will facilitate future high-quality research that will ultimately improve outcomes for all women seeking reconstructive surgery.

**Trial registration:**

ISRCTN37664281

## Background

Breast cancer affects 51,000 women each year in the United Kingdom (UK) [1] of whom approximately 40 % [2] will require a mastectomy. The loss of a breast may profoundly impact women’s quality of life [3], and immediate breast reconstruction (BR) is routinely offered to improve outcomes [4].

Implant-based breast reconstruction (IBBR) is the most commonly offered reconstructive procedure in the UK accounting for almost 40 % of all immediate BR performed following mastectomy for breast cancer [5]. Traditional subpectoral IBBR is performed as a two-stage procedure. This is necessary because the subpectoral pocket is too small to accommodate a definitive implant and expansion with a tissue expander is required as a first-stage. Multiple expansions with saline, which may be time-consuming and uncomfortable [6], are then needed before the final implant can be inserted at a second operation.

Over the last 10 years, the introduction of new techniques to augment the subpectoral pocket with biological or synthetic mesh or the patient’s own de-epithelised skin have revolutionised the procedure. The techniques, collectively referred to as lower-pole sling reconstructions (LPSR), may avoid the need for a tissue expander by facilitating single-stage direct-to-implant reconstruction [7] and improve cosmetic outcomes through better lower-pole projection [8–15]. Various products are available and vary widely in cost from £200 for a synthetic mesh such as TiLOOP® [16] or TIGR® Matrix [17] to £1900 for biological alternative [7, 18] such as an acellular dermal matrix (e.g. Strattice® or SurgiMend®). Product selection is currently dependent on surgeon preference.

Despite the rapid adoption of these techniques into routine practice, there have been no well-designed randomised controlled trials (RCTs) comparing them with each other or other BR procedures. One RCT has attempted to compare IBBR with and without a mesh, but closed prematurely due to poor recruitment [19]. Systematic reviews [20–27] have summarised non-randomised studies, but these are at a high risk of bias with significant methodological limitations and cannot be relied upon. A more recent review [28] has critically appraised the evidence and demonstrated a paucity of outcome data relating to the UK practice of single-stage LPSR with non-human biological and synthetic meshes. Comparative data are lacking. Outcomes from UK LPSR studies, however, suggest complication rates may exceed 30 % [29–32] compared the 11 % observed with standard IBBR in the National Mastectomy and Breast Reconstruction Audit [33]. There is therefore a need to robustly evaluate the outcomes of current approaches to IBBR to protect patients and provide evidence for health commissioners to support the provision of these procedures.

Randomised clinical trials provide the best evidence for the effectiveness of most interventions [34], but surgical trials are complex and the challenges to the conduct of well-designed, multi-centre RCTs are well-documented [34–43]. Clinical trials in BR are particularly problematic due to surgeon preference [44–55]. Over the last 20 years, only 14 BR RCTs have been conducted [19, 55–65] of which only four considered IBBR [19, 58, 59, 64]. Systematic reviews [66, 67] have highlighted the need for high-quality BR research but prevailing expert opinion suggests that BR RCTs would be ‘unethical’, ‘impractical’ and/or ‘inappropriate’ [49–53]. Recent qualitative work, however, suggests that well-designed BR RCTs that do not compromise patient choice may be acceptable [68], but identified a lack of understanding of pragmatic trial methodology among BR surgeons as a potential barrier to trial participation [44]. Exploratory, pre-trial work is therefore essential to determine the feasibility of undertaking a trial in IBBR and to inform the optimal study design.

The paucity of data regarding the current practice and outcomes of LPSR in the UK, however, presents particular challenges to the effective design of a pragmatic RCT. There is insufficient data to inform the selection of appropriate comparators, outcomes, sample size or selection criteria. It is also unclear how many patients may be eligible to participate. The need for high-quality data regarding the outcomes of LPSR is increasingly recognised [18, 69], but early progression to a poorly designed trial may alienate potential participants. A large prospective cohort study that engages surgeons, builds collaborations, develops understanding of the need for trials in IBBR and stimulates stakeholder investment in procedure evaluation while generating data to inform the design and conduct of a future trial is therefore necessary before a definitive pragmatic RCT can be initiated.

The National Trainee Research Collaboratives (NTRC) have emerged over the last 5 years as a novel, but effective model for delivery of high-quality multi-centre surgical research [70]. Originating in the West Midlands, the general surgery collaborative network now spans the entire UK [70] alongside subspecialist networks such as plastic surgery [71, 72]. This innovative model of trainees at different hospitals working together has an impressive track record in the design and delivery of large multi-centre cohort studies e.g. the appendicectomy study which recruited 3326 patients from 95 centres over 2 months [73–75] and high-quality surgical trials such as ROSSINI [76] (Reduction in Surgical Site Infection using a Novel Intervention) Trial which randomised 760 patients from 21 centres to a wound protection device versus standard care and recruited ahead of target. Trainees are highly motivated to participate and gain familiarity with research methodology whilst developing practical research skills such as recruiting patients to trials. Trainee networks have the potential to build research capacity and make a significant contribution to clinical research and as such are integral to the new Royal College of Surgeons surgical research infrastructure [70, 77]. This approach has yet to be established in breast and reconstructive surgery but may represent a time and cost-effective means of conducting high-quality research in this area.

## Methods/design

### Aims

The overall aims of the iBRA (implant breast reconstruction evaluation) study are to explore the feasibility, design and conduct of a pragmatic randomised controlled trial (RCT) comparing the effectiveness and cost-effectiveness of novel approaches to implant-based breast reconstruction (IBBR) and the feasibility of using the trainee collaborative model to deliver such a study in breast and reconstructive surgery.

### Study design

The iBRA study will have four phases:Phase 1 will evaluate current practice of implant-based breast reconstruction (IBBR) with a national practice questionnaire (NPQ).Phase 2 will prospectively examine clinical and patient-reported outcomes (PROMs) of IBBR and compare the outcomes of new approaches to surgery with published quality standards [78] and outcomes from the National Mastectomy and Breast Reconstruction Audit (NMBRA) [5, 33, 79, 80].Phase 3 will use mixed methods: an IBBR-RCT acceptability survey (IBBR-RCTAS) developed from phases 1 and 2 and qualitative semi-structured interviews to explore patients’ and surgeons’ attitudes to candidate trial designs and outcomes and their willingness to participate in a future RCT.Phase 4 will incorporate the findings of phases 1 to 3 to inform the design and conduct of a pragmatic definitive RCT with an internal pilot phase which will evaluate the effectiveness and cost-effectiveness of two types of IBBR.

### Phase 1 - National practice questionnaire (NPQ)

The aim of phase 1 is to understand current practice of IBBR in the UK to inform the design of the definitive RCT. This will be achieved with these objectives:i.To establish the number of centres and surgeons that perform IBBR and are able and willing to participate in a future trial.ii.To determine the incidence of each type of IBBR being performed at centre and surgeon level (informing trial design and sample size)iii.To examine how surgeons select suitable patients for surgery (informing the inclusion criteria of the trial)iv.To determine how the implant procedures are performed at centre level, especially how lower-pole coverage is achieved (informing trial design)v.To establish current practice of pre and post-surgical care in IBBR which will inform the use and standardisation of concomitant interventions in the trialvi.To engage surgeons to develop an appreciation of the need for RCTs in IBBR

#### Development of the National Practice Questionnaire

The questionnaire will be developed by members of the steering group. It will ask each centre for information on current IBBR practice (operations and approaches), the multi-disciplinary team in the unit (the type of staff and numbers), the use of novel techniques (dermal slings, biological and synthetic meshes and products used) and how patients are selected for procedure types (the role of neoadjuvant treatments, diabetes, smoking and body habitus). Information about the care pathway in each centre will also be collected.

#### Inclusion criteria for the NPQ

All breast and plastic surgical units performing mastectomy with or without BR in women in the UK will be eligible for inclusion.

#### Data collection in each participating centre

Trainees will be invited by e-mail to participate in the study through the Mammary Fold (MF) Breast Trainees’ Association, the National Trainee Research Collaborative (NTRC) and the Reconstructive Surgery Trials Network (RSTN). Trainees willing to act as the trainee lead for their centre will be asked to contact the study team to express their willingness to participate and to register their Unit. Unit participation and Trainee Lead status will then be confirmed by the study team and relevant documentation sent. Follow-up e-mails will be sent via the MF, RSTN and the professional associations to encourage study participation. Trainee leads will be responsible for identifying a supervising consultant and obtaining the support of other consultants in the Unit. This is the standard approach for NTRC projects which is acceptable and highly effective.

Local Trainee Leads will be responsible for completing the NPQ, paper-based or electronically, with the support of their supervising consultants.

The professional associations (Association of Breast Surgery, ABS and British Association of Plastic, Reconstructive and Aesthetic Surgeons, BAPRAS) have endorsed the study and will encourage Units to participate and support their trainees in recruiting patients and collecting data.

#### Sample size

The National Mastectomy and Breast Reconstruction Audit (NMBRA) [33] collected data from 156 acute Trusts performing mastectomy and BR surgery. Based on a 60 % participation rate, it is anticipated that 100 units may contribute to the study. The study team will approach breast and plastic surgical units via both trainees and the professional associations to maximise participation.

#### Questionnaire data analysis

Questionnaire data will be summarised and summary statistics reported to describe provision of care and practice of IBBR.

Categorical data will be summarised by counts and percentages. Continuous data will be summarised by mean, standard deviation and range if data is normally distributed. Median, interquartile range and range will be reported if the data is skewed. No formal statistical testing will be undertaken.

Where respondents’ free-text responses have been collected these will be anonymised. Thematic analysis will be performed and results presented alongside the quantitative analysis to help contextualise and illuminate them.

#### Feedback and surgeon engagement

Participating units will receive individualised feedback via reports giving their responses alongside cohort averages and national quality standards. This will highlight variation between local and regional practice and enable surgeons and units to compare their local practice to regional and national standards. It will also engage them in the project and highlight the need for a RCT to generate evidence-based practice for regional consistency.

### Phase 2 - Prospective cohort study of patients undergoing implant-based breast reconstruction

The aim of phase 2 is to document the practice and outcomes of IBBR in the UK to inform the design of a definitive RCT. This will be achieved with these objectives:i.To determine variation in the types of implant-based procedures performed at centre level, in particular, variation in techniques used to achieve lower-pole cover (informing trial design).ii.To evaluate the practicality of obtaining clinical and patient-reported outcome data across centres with little or no experience in participating in surgical trials, including the feasibility of working with trainees to recruit patients and collect longitudinal data (modelling this on experience in general surgical collaboratives [76]), with a view to using this approach in a future trial.iii.To compare the outcomes of different approaches of IBBR to published clinical standards and identify risk factors associated with adverse outcomes such as the impact of the learning curve (informing entry criteria, primary and secondary outcomes and parameters required for a power calculation).iv.To explore the variability of the BREAST-Q between procedure subtypes and hence its value for use in a future trial.v.To engage and educate consultants and trainees through regular feedback to create a culture of collaborative working and to establish an appreciation of the need for, and a desire to participate in, a future trial in IBBR.vi.To create the infrastructure to deliver a future trial by developing a network of breast and plastic surgical trainees trained in research methodology supported by consultant surgeons who will participate and recruit patients to surgical trials.

#### Methodology

Centres identified as performing immediate IBBR from the NPQ (phase 1) will be eligible to progress to phase 2, the prospective cohort study. The named supervising consultant will act as the principal investigator for each unit and trainee leads will be responsible for recruitment and data collection.

The study will be piloted in two centres (Liverpool and Bristol) prior to national roll-out to evaluate feasibility and effectiveness of trainee involvement in recruitment and data collection. Methods of data management will also be assessed.

#### Patient inclusion and exclusion criteria

All female patients electing to undergo immediate IBBR for malignancy or risk-reduction under the care of the breast or plastic surgeons will be eligible for inclusion in the study. Excluded will be women undergoing delayed IBBR, revisional surgery and those not able or willing to provide written consent (for patient-reported outcome measures (PROMs) part of the study).

#### Participation identification and recruitment

Potential participants will be identified prospectively by the local study team via clinics, local multi-disciplinary team meetings (MDTs), consultant surgeons and clinical nurse specialists. Simple demographics, procedure and process data will be collected for each participant. Data will be recorded in an anonymised format using a unique alphanumeric study identification number on a secure web-based database. In-hospital complication data will be collected prospectively by trainee leads. Patients will be reviewed in clinics at 30 days to collect complication and oncology data. Note that review will be performed in patients who do not attend for 30 day follow-up.

Trainees or a locally designated member of the team will approach patients in clinics or during their admission to obtain consent for PROMs assessment. Individual centres will be free to determine the optimal approach for recruiting patients to this part of the study. PROMs assessment will be by post or e-mail, dependent on patient preference, at 3 and 18 months (for those eligible for long-term assessment) following surgery and will evaluate satisfaction with care, complications and health-related quality of life (see details below). If consent is obtained, contact details will be sent securely to the co-ordinating centre and questionnaires distributed centrally to optimise compliance, allow accurate follow-up and reduce the incidence of missing data.

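### PROMs consent has no fixed time relative to surgery and the approach is left to each centre, so entry to the PROMs sample can depend on an early complication

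*Protocol article*

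**What the plan says.** All references are to Phase 2 of the protocol article.

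- **Where consent is sought, and who decides how.** Under Participation identification and recruitment, trainees or another local team member "will approach patients in clinics or during their admission to obtain consent for PROMs assessment. Individual centres will be free to determine the optimal approach" to recruitment for the PROMs part.
- **What consent controls.** Patient inclusion and exclusion criteria excludes "those not able or willing to provide written consent (for patient-reported outcome measures (PROMs) part of the study". Consent is therefore the condition of entry to the PROMs part.
- **What the questionnaires measure, and when.** They "will evaluate satisfaction with care, complications and health-related quality of life", and are sent "at 3 and 18 months (for those eligible for long-term assessment) following surgery". No questionnaire before surgery is described.
- **Clinical data.** "In-hospital complication data will be collected prospectively by trainee leads", and "Patients will be reviewed in clinics at 30 days to collect complication and oncology data". Neither sentence makes these data conditional on PROMs consent.

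**The concern.** Clinics are not limited to pre-operative ones; the same section uses the word for the 30-day review. An admission includes the post-operative stay. With no baseline questionnaire, nothing else forces consent before the operation. A woman can therefore be asked after a complication has occurred.

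The selection could run either way. A woman who is unwell or back in theatre may be missed or may decline. A centre that recruits at follow-up visits may see more of the women who keep returning with problems. Because the approach is local, the direction could also differ between centres.

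Three uses of the PROMs data are exposed:

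- **Patient-reported complications**, where selection would act on the measured outcome itself.
- **Information after 30 days.** Candidate outcomes run to 3 or 18 months (Study outcomes), and the questionnaire is the only later collection that the article describes.
- **Comparisons between centres or techniques.** Units receive feedback on local PROMs against the national standard (Feedback and surgeon engagement), and BREAST-Q is to be explored for its ability to separate procedure subtypes (Analysis, Patient-reported outcome measures). Technique is expected to vary by centre (Phase 2, objective i), so consent practice may be mixed up with technique.

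**Working it through.** **The plan's own figure.** The point disputes no figure, but the planned precision is a useful yardstick. For one proportion with p = 0.09 and half-width d = 0.04 (Sample size considerations):

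n = 1.96² × 0.09 × 0.91 / 0.04² = 196.6, rounded up to 197, as stated. With 15 % loss, 197 / 0.85 = 231.8, so 232. The article's target of at least 235 covers this.

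**Formula for selection.** Let p be the true complication rate, a the consent rate of women with a complication before the approach, and b the consent rate of all other women. If every complication precedes the approach, the rate among consenters is

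q = p·a / (p·a + (1 − p)·b).

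**Inputs.** The Background cites complication rates of 11 % for standard reconstruction and possibly over 30 % for the sling techniques. The documents give no consent rates by complication status, so a and b are assumed.

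| True p | a / b | Calculation | Rate among consenters |
|---|---|---|---|
| 30 % | 60 % / 80 % | 0.18 / (0.18 + 0.56) | 24.3 % |
| 30 % | 90 % / 70 % | 0.27 / (0.27 + 0.49) | 35.5 % |
| 11 % | 60 % / 80 % | 0.066 / (0.066 + 0.712) | 8.5 % |
| 11 % | 90 % / 70 % | 0.099 / (0.099 + 0.623) | 13.7 % |

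**Why these are upper illustrations.** If only a fraction f of complications precede the approach, the others carry consent rate b. In the formula, a is then replaced by f·a + (1 − f)·b. At f = 1 the table applies; at f = 0 the replacement equals b and q = p, so there is no bias. The documents do not give f.

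**Against the planned precision.** Write r = a/b. For a true 9 %, the r that moves the apparent rate to a limit q of the planned interval is r = q(1 − p) / (p(1 − q)):

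- q = 0.05: 0.05 × 0.91 / (0.09 × 0.95) = 0.53
- q = 0.13: 0.13 × 0.91 / (0.09 × 0.87) = 1.51

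Only a strong imbalance reaches the planned half-width of 4 points. At r = 0.8 the apparent rate is 0.072 / (0.072 + 0.91) = 7.3 %. Recruiting more women does not reduce such a bias.

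**BREAST-Q.** Assume a within-group SD of 20, a 30 % complication rate, a deficit of up to 20 points after a complication, and r from 0.5 to 1.5. The share with a complication then runs from 0.15 / 0.85 = 17.6 % to 0.45 / 1.15 = 39.1 %.

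- Mean shift: −20 × (0.1765 − 0.30) = +2.5 points, to −20 × (0.3913 − 0.30) = −1.8 points.
- SD = √(400 + q(1 − q) × 20²): 22.0 with no selection, 21.4 at r = 0.5 and 22.25 at r = 1.5. The change is less than 1 point.

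**The case against.** **The text does not say that consent is post-operative.** Eligibility is framed around women choosing to have surgery, and participants are identified prospectively, so a pre-operative approach is at least as natural a reading. Recruitment at the 30-day review is an inference, since that review is named only for complication and oncology data. Centres are given the approach, not expressly the timing. All of this is fair. What stands is that the article permits consent after an early complication and nothing in it rules that out.

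**The clinical end-points are not the PROMs.** The likely primary outcome is a clinical effectiveness end-point, and patient-reported complications are not listed as a candidate. Sample size considerations also intends follow-up of all women to 3 months. A reader might infer that the study's complication data as a whole are selected. The documents do not support that, because in-hospital and 30-day clinical complications are not stated to depend on PROMs consent.

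**Flexibility has a purpose.** This is a feasibility cohort in centres with little trial experience, piloted in two centres, and the subtype comparisons are exploratory. That argues against a rigid rule. It does not argue against a default with a fallback.

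**Reporting detail usually sits elsewhere.** A date field and tabulations are commonly left to the full protocol, case report form or analysis plan, none of which is shown. Their absence is not the point here. The point is the recruitment rule that the article does state; the field and the table serve to show its effect.

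**Conclusion.** The point holds for the PROMs sample. Consent may follow an early complication, so entry to that sample can depend on it, and the dependence can differ between centres. It is a cheap improvement and does not invalidate the plan.

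Direction and size cannot be derived from the documents. Under the assumed consent rates a true 30 % would appear as 24 % or 36 %, and a true 11 % as 8.5 % or 13.7 %. All four results assume that every complication precedes the approach, so they are upper illustrations for those consent rates.

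Two stronger readings are tempting and not supported:

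- **Otherwise identical centres would differ by 10 points or more.** That sets opposite assumed scenarios against each other at the 30 % rate. At 11 % each shift is under 3 points.
- **The BREAST-Q SD needed for the trial's sample size would be materially biased.** Under the assumptions shown it moves by less than 1 point. The mean moves by up to about 2.5 points.

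**What to change.** In Participation identification and recruitment, make the pre-operative contact the default time for PROMs consent at every centre, allow later consent as a fallback, and record the consent date. Women are already identified prospectively through clinics and multi-disciplinary meetings, so the default fits the existing route.

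Report PROMs consent and questionnaire return by in-hospital and 30-day complication status and by procedure type. As described, the clinical data are collected without PROMs consent, so consenters and non-consenters can be compared. Study status shows that recruitment is under way. The default can apply only to women still to be approached, but the table can cover the whole cohort and would show whether selection occurred.

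The cost is one protocol sentence, one date field and one table. The downside is slightly less freedom for centres and perhaps a few missed consents where pre-operative contact is short; the fallback limits that loss.
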